#### Plans to give access to the full protocol, participant-level data and statistical code {31c}

The full protocol (French version) is available upon request to the authors. No participant-level data will be shared.

### Oversight and monitoring

#### Composition of the coordinating center and trial steering committee {5d}

This study is promoted and coordinated by the Direction of Clinical Research and Innovation (DRCI) of Hospices Civils de Lyon, France. This structure includes dedicated Clinical Research Associates, who will monitor the study upon EudraLex practice guidelines.

#### Composition of the data monitoring committee, its role, and reporting structure {21a}

The data monitoring committee is a part of the institutional Research Department, and is independent from the sponsor; it has no competing interests regarding the study.

#### Adverse event reporting and harms {22}

The nature of the study (education intervention) is not intended to produce any harm. However, at the last visit, any potential adverse effect will be collected by the responsible surgeon.

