### Objectives {7}

We hypothesize that an educational intervention based on the rational perception of postoperative pain and discomfort, and the proper use of analgesics would improve the quality of pain management at home and reduce analgesics-related side effects.

The study evaluates the effectiveness of an educational intervention on pain relief at home in outpatient orthopedic surgery, compared to standard care. The pain relief is assessed during the first five post-discharge days (primary outcome), then on the 10th, 20th and 30th days after surgery (secondary outcome). The prevalence of severe pain (as reported by participants), medication use, side effect of medication, changes in sleep quality, the incidence of neuropathic pain at day 30 after surgery, and overall satisfaction at day 30 will be assessed as a part of secondary objectives.

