### Strategies to improve adherence to interventions {11c}

Instructions about the purpose of the study and the importance to fill in and to return the diary are thoroughly provided during the inclusion visit. Participating patients will receive a text message via their private e-mail or phone (short message service, SMS) on the day, where their action to fill in the diary is necessary (day 0–day 5, days 10, 20, and 30). The last message on day 30 contains instructions on how to return their diary. Patients are expected to bring the filled diary on day 45 (scheduled surgical visit) or send it by post. Patients are provided with prepaid envelopes in order to send the diary if no postsurgical visit is scheduled on day 45.

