### Relevant concomitant care permitted or prohibited during the trial {11d}

Participants are provided with a standard pain treatment order including acetaminophen, ketoprofen, and weak opioids. They are allowed to use any additional medication or non-pharmacological pain relief, in such cases, this should be traced in the diary. In France, the access to non-steroid and opioid analgesics is highly regulated, so the chance that enrolled patients will considerably modify their home treatment is weak. Hypothetically, patients hospitalized during the follow-up period, or deceased, will be considered as lost for follow-up and therefore excluded.

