### Participant timeline {13}

Patients are followed for 30 days after the discharge from the hospital (Table 1).

**Table 1 Tab1:** Timeline for patients included in the trial

Actions	Days of study										
	–30 to 0	Surgery	1	2	3	4	5	10	20	30	45
Inclusion/exclusion criteria check	X										
Information and written consent signed	X										
Randomization	X										
Neuropathic pain evaluation	X									X	
Sleep Quality Evaluation	X									X	
International Pain Outcome Questionnaire										X	
At-home diary : - Pain relief, % - Medication taken - Side effects		X	X	X	X	X	X	X	X	X	
Recall SMS/email			X				X	X	X	X	
Diary collection											X

*SMS* short message service

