### Data collection and management

#### Plans for assessment and collection of outcomes {18a}

A dedicated electronic case report form (e-CRF) within Ennov Clinical® software was created and managed by Clinical Research Department, Hospices Civils de Lyon. The following data are collected upon inclusion: demographics, type of surgery, type of anesthesia, assessment of neuropathic pain with DN4, and assessment of the sleep quality with PSQI. After the discharge, patients fill in the dedicated diary. The prevalence of severe pain (which patients deem to be important) (binary), pain relief (continuous), painkiller administration (binary), and side effects from painkiller (binary) are collected in a time-dependent manner with 30 min grid over 24 h. On day 30, patients fill in the assessment of neuropathic pain with DN4, assessment of the sleep quality with PSQI, and the International Pain Outcome questionnaire (multiple binary, categorical and continuous variables). After the diary completion, patients were asked to send the collected data to the investigators.

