### Statistical methods

#### Statistical methods for primary and secondary outcomes {20a}

Analyses will be performed on an intention-to-treat basis. All data will be checked for normal distribution, and variables will be presented as mean ± standard deviation (SD) or as the median and interquartile range [IQR] accordingly. Categorical variables will be presented as the number and percentage of the total. To compare the two groups, we will use Fisher’s exact test for qualitative data and the non-parametric Mann-Whitney tests for quantitative variables. A comparison of the two groups at randomization will identify potential bias due to unequal allocation. A multivariate logistic regression analysis will be performed to study conditions independently associated with the response to the intervention and to control potential confounding factors. A 0.05 *p* value will indicate statistical significance. Statistical analyses will be performed using R software (R Foundation for Statistical Computing, Vienna, Austria).

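### Patients hospitalised or deceased during follow-up are excluded despite intention to treat, which removes the most serious events from the harms comparison; other non-analgesic adverse effects depend on a last visit that some patients may not have at day 45

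*Protocol article*

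**What the plan says.** Five parts of the protocol article bear on harms.

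- **Exclusion.** Section {11d} (concomitant care) states: "patients hospitalized during the follow-up period, or deceased, will be considered as lost for follow-up and therefore excluded". The sentence presents these cases as hypothetical, but the rule itself is definite.
- **Analysis principle.** Section {20a}: "Analyses will be performed on an intention-to-treat basis".
- **General adverse effects.** Section {22} remarks that an educational intervention is not meant to cause harm, then says that "at the last visit, any potential adverse effect will be collected by the responsible surgeon".
- **The last visit.** Section {11c} identifies day 45 as a surgical visit: "Patients are expected to bring the filled diary on day 45 (scheduled surgical visit) or send it by post". It adds: "Patients are provided with prepaid envelopes in order to send the diary if no postsurgical visit is scheduled on day 45". At day 45, Table 1 lists diary collection and nothing else.
- **Painkiller side effects.** These have their own route. The objectives in {7} list "medication use, side effect of medication, changes in sleep quality" among the secondary aims. Section {18a} says that "side effects from painkiller (binary) are collected in a time-dependent manner with 30 min grid over 24 h". The diary row of Table 1 reads "At-home diary : - Pain relief, % - Medication taken - Side effects" and is marked for the day of surgery and days 1 to 5, 10, 20 and 30.

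**The concern.** The trial tests whether education on pain and analgesic use improves pain management at home and reduces analgesic side effects. The abstract gives emergency calls and readmissions after discharge as part of the problem. A patient admitted because of an analgesic complication is therefore among the most informative for the harms question, and {11d} excludes that patient. Allocation is known to patients, physicians and data managers ({17a}), so an exclusion triggered by a post-randomisation event has no blinding to protect it.

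The second worry is coverage. If the surgeon's question at the last visit is the only described route for events other than painkiller side effects, anyone without that visit has no described route for them. At stake is whether the trial can say anything dependable about serious or non-analgesic harm by arm.

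**Working it through.** The article gives no harms figure to reproduce, so the check sets the sections side by side.

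**Step 1: {11d} against {20a}.** Intention to treat keeps every randomised patient in the arm assigned. Section {11d} removes patients for something that happens after randomisation. Both cannot hold for the same analysis, and the article does not limit either statement to particular outcomes.

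**Step 2: what the exclusion does to a harms table.** If every patient hospitalised or deceased during follow-up is excluded, the number of such events among those retained is 0 in the intervention arm and 0 in the control arm, whatever the true counts. A real difference between arms in these events could not appear. Side effects that these patients entered in the diary before the event would leave with them.

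**Step 3: interaction with replacement.** Section {20c} replaces patients whose data for the first three days are missing. An early admission that interrupts the diary could therefore end in replacement by a new recruit as well as exclusion.

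**Step 4: which adverse effects depend on the last visit.**

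| Type of event | Route described | Needs a visit? |
|---|---|---|
| Painkiller side effects | Diary ({18a}, Table 1) | No; the diary can be posted ({11c}, {18b}) |
| Any other adverse effect | Surgeon at last visit ({22}) | Yes |
| Hospitalisation, death | Excluded ({11d}) | Not applicable |

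The diary covers the day of surgery, days 1 to 5, and days 10, 20 and 30: 1 + 5 + 3 = 9 days. Days 0 to 30 number 31, so 31 − 9 = 22 days have no diary page. Neither {18a} nor Table 1 describes a diary item for events other than painkiller side effects.

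**Step 5: who may miss the last visit.** The prepaid-envelope provision in {11c} anticipates patients with no surgical visit at day 45, but does not say how many. Posting the diary is also open to patients who do attend, so the number of posted diaries would not measure the number of missed visits.

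**Step 6: size.** An undercount would need the rates of hospitalisation, death and missing last visits, and the incidence of non-analgesic adverse effects. The article gives none of these, so no figure is offered.

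**Step 7: how far a new diary item could reach.** The trial status section reports 256 recruited. Against the 410 in {14}, 410 − 256 = 154 remained, and 256/410 = 62% were already in. Against the 414 in the abstract, 414 − 256 = 158 remained, and 256/414 = 62%.

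**The case against.** A reader might infer that adverse effects are collected only by the surgeon at the last visit, and that harms are therefore undercounted. The documents do not support either statement. Painkiller side effects, the harm in the hypothesis and the secondary objectives, are recorded by patients in both arms in a diary that needs no visit. A missed day-45 visit leaves that record intact.

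The other side can add more:

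- The wording in {11c} is conditional. It does not say that any given patient lacks surgical follow-up, and {22} refers to the last visit without naming day 45, so a visit on another date would fit.
- Section {11d} calls hospitalisation and death hypothetical, and does not say that adverse events in these patients go unrecorded.
- Emergency calls and readmissions are background in the abstract and are not listed as outcomes in {12}.
- The article condenses a fuller French protocol, which may hold detailed adverse-event procedures.

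Most of this stands against the broad reading. It reduces the visit gap to a possibility that affects non-analgesic events in an unknown number of patients. It does not remove the conflict between {11d} and {20a}. That is a stated rule, not detail left out for brevity, and its being rarely invoked does not make it compatible with intention to treat. Events recorded somewhere but excluded from the comparison by arm would still be absent from the trial's harms result.

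**Conclusion.** The point holds in two parts of unequal weight.

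The main part is firm: {11d} conflicts with {20a} and, followed as written, removes hospitalised and deceased patients from the comparison by arm because a serious event occurred. This assumes that exclusion there means exclusion from the analysis, which is its natural reading.

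The lesser part is a risk: adverse effects other than diary-recorded painkiller side effects may be undercounted in patients with no last visit. This assumes that some patients covered by the envelope provision have no later surgical visit, and that no other route exists.

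The size of either effect cannot be computed from the document. Hospitalisation and death may prove rare in elective outpatient arthroscopic and ligament surgery, but the article gives no rate to confirm it.

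**What to change.** 1. Amend {11d} so that patients hospitalised during follow-up, or deceased, stay in the harms tabulation in their randomised arm. Use their diary data up to the event and count the hospitalisation or death as an event. Apply the same to any patient replaced under {20c}.
2. Reconcile {11c}, {11d}, {20a} and {22}, so that the analysis population, the meaning of the last visit and the route for patients without one are stated consistently.
3. For patients with no last visit, ask about adverse effects and hospitalisation through contacts that already exist: the day-30 diary page for those still to be enrolled, and the coordinator's contact with non-returners in {18b}. Use the same wording in both arms.

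**Cost.** The first two changes are wording amendments and can cover patients already enrolled whose events are known. The third adds a question to a diary page and to an existing contact, with no new visit. Its limit is timing: with 256 patients recruited at manuscript revision, most of the target would lack the new diary item. The coordinator contact reaches only those who have not returned a diary, so an already enrolled patient who posted the diary and had no visit would be reached by neither. The new item should be reported as partial, with the number of patients asked in each arm.

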#### Frequency and plans for auditing trial conduct {23}

At least 10 monitoring sessions are scheduled—before the first inclusion, every 50 inclusions, and after the last inclusion.

#### Plans for communicating important protocol amendments to relevant parties (e.g., trial participants, ethical committees) {25}

A formal amendment to the protocol will be made for any changes to the protocol that may affect the study (objectives, endpoints, design, participants population, sample sizes, procedures, or significant administrative aspects). These changes will be reported to relevant parties (e.g., trial registry, ethics committee).

#### Dissemination plans {31a}

The results of the trial will be disseminated through international scientific conferences and submitted to highly ranked peer-reviewed journals for publication. The findings will also be shared through regional, national, and international scientific and practical meetings.

## Discussion

PELOPS is a randomized controlled trial comparing a structured educational intervention to a control group that receives standard information on pain self-management at home after discharge from orthopedic outpatient surgery. The primary outcome measurement is focused on the time-dependent variable—TOTPAR score as the most sensible, and not on summarizing pain intensity assessment [46], with a clinically significant threshold [43]. A post-discharge burden incurred by patients at home (side effects of treatment, sleep changes, IPO) is assessed as well, because of its importance [42, 47].

Current evidence does not demonstrate a clear effect of preoperative patient education on outpatient pain control. Paucity and methodology weakness (heterogeneous primary outcomes, unclearly defined population, unclearly described intervention) of published studies preclude the inference [12, 13]. Although not blinded (impossible to mask the intervention), this will be the first to our best knowledge randomized study, using meaningful measurement to evaluate the effectiveness of a standardized educational intervention on pain relief at home. Our intervention targets pain relief, independent and universal outcome, and not focused on a specific type of procedure.

Rising popularity of minimally invasive surgeries, thorough selection of patients, and availability of high-quality short-acting anesthesia has led to a dramatic decrease in hospital stay for numerous procedures. The low-risk complications and benefits associated with reduced cost and less hospital stay have driven the growth of the market. Arthroplasty, spine fusion, colorectal resection, and open prostatectomy—procedures associated with important potential for postoperative pain—are more and more performed in ambulatory settings (49). Our study will contribute to the growing evidence base for non-pharmacological pain treatment optimization, as we do not modify surgical analgesics prescriptions. If the study hypothesis is supported, the findings will provide the evidence and the base for educational intervention development in other than orthopedics specialties. As our intervention is not specialist-based, a wide range of clinicians can provide it, individually or in groups, before surgery.

## Trial status

At the date of the manuscript revision, the protocol version 4 from 29/12/2020 was effective. A total of 256 patients were recruited.

## Data Availability

The data generated for the final analysis will be stored electronically at the Center of Clinical Research, Hospices Civils de Lyon-France. The full protocol and statistical code will be accessible upon request from the Principal investigator (MD). Participant-level data will not be shared.

## Abbreviations

ANSM: Agence nationale de sécurité du médicament et des produits de santé
DN4: Douleur Neuropathique 4
DRCI: Direction de la Recherche Clinique et Innovations
e-CRF: Electronic case report form
IPO: International Pain Outcome
IQR: Interquartile range
MPFL: Medial patellofemoral ligament
OR: Odds ratio
PELOPS: Preoperative Education for Less Outpatient Pain after Surgery
PRO: Patient-related outcome
PSQI: Pittsburgh Sleep Quality Index
SFAR: Société Française d'Anesthésie et de Réanimation
SMS: Short message service
TOTPAR: Total pain relief
